#### CT feasibility and acceptability outcomes

Feasibility of the digital CT is assessed in terms of participants’ ability to complete the intervention as prescribed. Indicators include CT dropout rate, number of training days completed, total duration of training, and technical handling, including any problems encountered during CT intervention. These data are collected from the CT software and via a pen-and-paper CT diary distributed to participants of the EG after their baseline assessment. Based on current literature, the CT intervention is considered feasible if CT dropouts are ≤ 14% [43] and participants completed at least 80% (i.e., ≥ 16/20) of the training days and the total training duration (i.e., ≥ 720/900 min) [30, 84]. Via optional free-text comments in the CT diary, participants can give qualitative feedback on technical handling of the CT (cf. next paragraph).

CT acceptability is evaluated based on participants’ experience with the CT. In the pen-and-paper CT diary, daily ratings capture the motivation to engage in CT on a 5-point scale (0 = “not motivated at all,” 5 = “highly motivated”) and satisfaction with each session (0 = “not good at all,” 5 = “very good”). Weekly ratings assess how well participants were able to integrate CT into their daily routines and the extent to which external factors, such as tiredness or stress, impacted training (0 = “not at all,” 5 = “very much”). At the end of the CT intervention, participants provide an overall evaluation using the German grading system (1 = “very good,” 6 = “unsatisfactory”) and indicate if they would recommend the CT (“yes”/“no”). Optional free-text comments are collected after each session, weekly, and in the final evaluation to capture qualitative feedback. The intervention is considered acceptable if the average scores across CT sessions and weekly ratings are ≥ 4/5 points and the overall evaluation reaches a score of ≥ 3.5/6 points according to the German grading system. Additionally, if more than 80% of participants recommend the CT, it will be considered acceptable. If the criteria for feasibility and acceptability are not met, the results of the CT efficacy should be interpreted cautiously as the intervention may not have been delivered effectively.

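### The grade criterion for acceptability is reversed as written, and the ≥ 4/5 rule counts a rating of interference with training as favourable

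*Protocol article*

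**What the plan says.** All the relevant text is in one section of the protocol article, CT feasibility and acceptability outcomes.

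- **Final grade.** The diary ends with an "overall evaluation using the German grading system (1 = “very good,” 6 = “unsatisfactory". Low is therefore good. The criterion is that "the overall evaluation reaches a score of ≥ 3.5/6 points according to the German grading system".
- **Daily and weekly ratings.** Motivation and satisfaction are rated each training day, with high values favourable (motivation: "0 = “not motivated at all,” 5 = “highly motivated"). Each week participants rate how well training fitted into daily life and "the extent to which external factors, such as tiredness or stress, impacted training (0 = “not at all,” 5 = “very much". The criterion is that "average scores across CT sessions and weekly ratings are ≥ 4/5 points". No item is excepted and no recoding is mentioned.
- **Recommendation.** A separate sentence, opening with the word Additionally, calls the training acceptable if more than 80% would recommend it.
- **Consequence.** If the feasibility and acceptability criteria are missed, "the results of the CT efficacy should be interpreted cautiously as the intervention may not have been delivered effectively".

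Acceptability is a stated hypothesis under Objectives {7} and a secondary outcome under Outcomes {12}.

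**The concern.** A prespecified threshold should sort results in the intended direction when applied literally. Here the grade threshold names the same scale whose anchors were just given, yet it asks for a value at or above the cut on a scale where low is good. The ≥ 4/5 rule then takes in a weekly item for which 5 is the worst answer, so greater interference moves the average towards acceptability.

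Two things are at stake. The second objective is partly judged by these criteria. The article also ties them to how the efficacy result should be read. If the direction, the pooling and the combination rule are settled only after the diaries have been summarised, the acceptability conclusion will look chosen after the fact.

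**Working it through.** The cut-offs are decision rules, not outputs of a formula, so there is no plan figure to reproduce. The check applies each rule literally and then with the direction corrected.

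**1. Grade criterion.** Inputs: scale 1 (best) to 6 (worst); threshold ≥ 3.5.

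| Mean grade | As written (≥ 3.5) | Reversed (≤ 3.5) |
|---|---|---|
| 1 | fails | meets |
| 2 | fails | meets |
| 3 | fails | meets |
| 3.5 | meets | meets |
| 4 | meets | fails |
| 5 | meets | fails |
| 6 | meets | fails |

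Recoding the grade as 7 − grade and keeping ≥ 3.5 is the same as ≤ 3.5 on the original scale, since 7 − g ≥ 3.5 means g ≤ 3.5. No such recoding is stated. Apart from the boundary value, every grade is classified the opposite way.

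**2. External-factors item.** Notation: M motivation, S satisfaction, I integration, E external factors, each 0 to 5. High is favourable for M, S and I, and unfavourable for E. The best possible profile is M = S = I = 5, E = 0. The text does not fix how ratings are averaged, so the range is shown:

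| Averaging (assumed) | Formula | Best profile | ≥ 4? | Effect of one more point of E |
|---|---|---|---|---|
| E judged alone | E | 0 | no | +1 |
| Two weekly items | (I + E)/2 | (5 + 0)/2 = 2.5 | no | +0.5 |
| Four types, equal weight | (M + S + I + E)/4 | 15/4 = 3.75 | no | +0.25 |
| Weighted by count: 20 sessions × 2, 5 weeks × 2 | [20(M + S) + 5(I + E)]/50 | (200 + 25 + 0)/50 = 4.5 | yes | 5/50 = +0.1 |

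The count weighting assumes every rating is given. With integration at its maximum, the two-item average reaches 4 only if (5 + E)/2 ≥ 4, that is, E ≥ 3.

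The sign of the last column is the same in every row: more interference raises the score. The direction can still decide the outcome under count weighting. Take M = S = I = 4:

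- E = 1: (160 + 20 + 5)/50 = 3.7, which fails. Reverse-scored (5 − 1 = 4): (160 + 20 + 20)/50 = 4.0, which meets.
- E = 5: (160 + 20 + 25)/50 = 4.1, which meets. Reverse-scored (5 − 5 = 0): (160 + 20 + 0)/50 = 3.6, which fails.

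With reverse scoring, the best profile averages 5.0 under all four schemes.

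**3. Combination with the 80% sentence.** Two readings are possible: a further requirement, or a sufficient alternative.

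- Mean grade 1, rating averages taken as met, 100% recommending: not acceptable if the 80% item is a further requirement; acceptable if it is an alternative.
- Mean grade 6, session and weekly averages of 4: acceptable under the alternative reading even with 0% recommending; acceptable under the requirement reading only if more than 80% recommend.

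So the reading of that sentence can change the overall verdict.

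**The case against.** **The grade is only one element.** The same sentence requires averages of ≥ 4/5 on ratings that include motivation and satisfaction, both correctly oriented. A disliked training would be expected to score low there. If more than 80% recommending is sufficient by itself, a well-liked training is accepted whatever the grade clause says. This stands. A reader might infer that a popular training will be declared unacceptable and an unpopular one acceptable. The article does not support that as a general result, because the overall verdict rests on the other ratings and on an unresolved combination rule.

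**Item scoring belongs in the full protocol or analysis plan.** Reverse-coding and averaging are details that a condensed article may leave out. This has some force for the external-factors item, where the size of the problem depends on unstated pooling and the best profile can even pass at 4.5. It does not rescue the grade criterion. There the article states a direction, and states it against its own anchors. An analysis plan that copied it would inherit the error, and one that corrected it would contradict the article.

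**The intended meaning is obvious.** Grade 3.5 or better is probably what was meant, since the anchors are printed in the same section. But the text does not say so, and a decision rule should not depend on the analyst's guess.

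**The 80% sentence may simply add a criterion.** The following sentence refers to the criteria collectively, which favours a joint reading without settling it. It would be wrong to assert that all criteria must hold jointly; the sponsor has to say.

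**Little depends on it.** Acceptability does not enter the primary MoCA contrast, the sample size or the per-protocol definition, which uses completed training days. This stands. A reader might infer that the efficacy result itself is compromised. It is not: no estimate or test changes, only the stated caution in interpreting it.

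**Conclusion.** The grade criterion is wrong as written. Mean grades below 3.5 fail it, grades from 3.5 to 6 meet it, and nothing elsewhere in the article corrects this. The conclusion needs no assumption beyond the printed anchors and threshold.

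The external-factors item runs the wrong way under the ≥ 4/5 rule in all four averaging schemes examined, but its weight is uncertain. Whether the best possible profile meets or fails the rule depends on a pooling choice the article does not state. This part assumes that the reference to weekly ratings includes both weekly items, as the wording does without exception.

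Both statements concern individual criteria, not the overall acceptability verdict. The consequence is confined to a secondary outcome and the caution attached to reading efficacy. Calling a scale from 0 to 5 a 5-point scale is a clerical slip (it has six levels) and changes no threshold.

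**What to change.** Before diary data are analysed:

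1. Change the grade criterion to mean grade ≤ 3.5, stating that 1 is best.
2. Reverse-score the external-factors item (5 minus the score), or take it out of the acceptability average and report it descriptively. State at the same time whether ratings are judged by item, pooled with equal weight, or pooled by count.
3. Have the sponsor state whether more than 80% recommending is a further requirement or a sufficient alternative.

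The 5-point label can be checked against the printed diary in the same edit. If an analysis plan already contains the right scoring, the article and the plan need to be brought into line.

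The cost is wording only: no new data, no change to the diary and no effect on the primary analysis. Trial status gives the end of 2025 as the expected close of recruitment, so the correction should be dated and made promptly, ahead of any diary summary.

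### The overall-grade component of the acceptability rule points the wrong way: 1 is the best grade and 6 the worst, yet the rule asks for at least 3.5

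*Protocol article*

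**What the plan says.** Everything needed is in one paragraph of the protocol article, in the section on CT feasibility and acceptability outcomes.

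- **The scale.** At the end of the training, "participants provide an overall evaluation using the German grading system (1 = “very good,” 6 = “unsatisfactory" being the two anchors. Lower is better.
- **The cut-off on that scale.** Acceptability requires that "the overall evaluation reaches a score of ≥ 3.5/6 points according to the German grading system".
- **The condition joined to it by 'and'.** "The intervention is considered acceptable if the average scores across CT sessions and weekly ratings are ≥ 4/5 points". Among these ratings is "satisfaction with each session (0 = “not good at all,” 5 = “very good" as its top anchor, so here higher is better.
- **A further sentence.** "Additionally, if more than 80% of participants recommend the CT, it will be considered acceptable".
- **The consequence.** "If the criteria for feasibility and acceptability are not met, the results of the CT efficacy should be interpreted cautiously".

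The article nowhere says that the final grade is recoded before it is compared with 3.5.

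**The concern.** The cut-off treats a high score as a good one. That suits the motivation and satisfaction ratings, which run from 0 to 5 with 5 best. The final grade runs the other way, so a score of 3.5 or more is the worse half of the scale. The direction was probably carried over from the diary ratings.

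Acceptability belongs to the trial's second objective (Objectives {7}) and is a named secondary outcome (Outcomes {12}). The criterion is a threshold fixed in advance, and it has a consequence: if the criteria are not met, the efficacy findings are to be read with caution because the intervention may not have been delivered effectively. A threshold that fails good grades can attach that caution for no reason. Correcting it once the grades are known would mean changing a fixed criterion with the result in view.

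**Working it through.** There is no computed figure to reproduce. The check is to apply the rule as printed and see what it returns.

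**Inputs**, all from the section on CT feasibility and acceptability outcomes: grade g from 1 (best) to 6 (worst); cut-off g ≥ 3.5; diary averages of at least 4 out of 5, joined by 'and'; more than 80% recommending the training, introduced by 'Additionally'. I assume that the cut-off applies to the mean grade across participants, which the article does not spell out.

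**Step 1: the grade component alone.** The midpoint of the scale is (1 + 6)/2 = 3.5. Reverse-scoring replaces g by 7 − g, and 7 − g ≥ 3.5 is the same condition as g ≤ 3.5.

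| Mean grade g | As printed, g ≥ 3.5 | Reversed, g ≤ 3.5 | 7 − g | 7 − g ≥ 3.5 |
|---|---|---|---|---|
| 1.0 | fails | meets | 6.0 | meets |
| 2.0 | fails | meets | 5.0 | meets |
| 3.0 | fails | meets | 4.0 | meets |
| 3.4 | fails | meets | 3.6 | meets |
| 3.5 | meets | meets | 3.5 | meets |
| 4.0 | meets | fails | 3.0 | fails |
| 5.0 | meets | fails | 2.0 | fails |
| 6.0 | meets | fails | 1.0 | fails |

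The printed and reversed criteria agree only at exactly 3.5.

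**Step 2: the grade together with the diary ratings.**

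| Diary averages | Mean grade | Joint rule as printed | Joint rule with g ≤ 3.5 |
|---|---|---|---|
| at least 4 | 2.0 | not met | met |
| at least 4 | 5.0 | met | not met |
| below 4 | 2.0 | not met | not met |
| below 4 | 5.0 | not met | not met |

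The error changes the joint verdict only when the diary averages reach 4. In that case a good final grade is what one would expect, so the first row is the likely one: a training that is liked on both measures fails. The second row needs participants who rate their sessions highly and then give a grade in the worse half of the scale, which is hard to picture.

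**Step 3: the recommendation sentence.** It can be read in two ways.

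- As a separate sufficient route, a training that more than 80% recommend is acceptable whatever the grade component says. The error is then masked for a well-recommended training.
- As a further requirement, it rescues nothing, and the well-graded training still fails.

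The wording does not settle which is meant. The grade component is inverted under both readings.

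**The case against.** The best defence is that the intended meaning is easy to guess. The anchors are printed in the same paragraph, reaching a score can be heard as meaning that score or better, and anyone who saw a unanimous top grade fail would notice at once. That makes lasting damage unlikely. It does not make the criterion right: the cut-off is tied by name to the German grading system, no recoding is given, and both the anchors and the inequality are intact running text, so faulty PDF extraction does not explain it. An analysis plan that is not shown might state the direction correctly, but the article would still print the opposite.

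The defence is stronger on consequences, and there it stands. A reader might infer that a disliked training would be declared acceptable and so support the adoption into daily life that the Discussion describes. The document does not support that. The diary averages must also reach 4 out of 5, and they include motivation and satisfaction, which a disliked training would be expected to miss. The Discussion also makes its statement conditional on feasibility, which has its own thresholds for dropout, training days and training time.

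A reader might equally infer that the acceptability rule as a whole returns the reverse verdict. That goes too far as well: when the diary averages are below 4 the verdict is the same under either direction, and the recommendation sentence may be a route by which a well-liked training is accepted anyway.

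Finally, the reach is limited. Neither the mixed model for the MoCA ({20a}) nor the per-protocol definition ({20c}), which rests on valid assessments and training days, uses the grade.

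**Conclusion.** The concern holds for the grade component. As printed, every mean grade better than 3.5 fails it and every mean grade worse than 3.5 meets it. The practical harm is that a well-graded training fails the joint rule and wrongly triggers the caution on the efficacy results. That harm is certain if the recommendation sentence is a further requirement, and avoidable if it is a separate sufficient route and more than 80% recommend the training.

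This should be fixed, but it is not critical. It affects one component of a secondary acceptability rule and the wording around efficacy; no estimate, test or analysis population of the primary outcome changes. The conclusion rests on two assumptions: that the cut-off applies to the mean grade, and that the grade is not recoded, since no recoding is stated. That the authors meant 3.5 or better is an inference. The midpoint arithmetic shows that flipping the inequality and reversing the score agree with each other, not what was intended.

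**What to change.** Before the final evaluations are summarised, replace the criterion by one of two equivalent forms:

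- mean overall grade ≤ 3.5, with 1 = very good and 6 = unsatisfactory; or
- reversed score, 7 − mean grade ≥ 3.5, with the reversal written out.

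The sponsor should confirm that 3.5 is the intended cut-off, and any analysis plan should carry the same direction. In the same edit, two neighbouring points need a sentence each: whether the recommendation criterion is a separate route or a further requirement, and whether the weekly item on how far tiredness or stress affected training is meant to fall under the 4-out-of-5 threshold. That item is scored with 5 as the strongest impact, so a high value there is unfavourable.

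The cost is a small text change, with no new data and no effect on participants. Trial status gives protocol version 6.0 of 26 November 2025, with recruitment expected to end by the close of 2025, so a dated correction should be made promptly.

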### Plans to promote participant retention and complete follow-up {18b}

Besides all measures taken to improve CT adherence for participants in the EG (see Sect. “Strategies to improve adherence to interventions {11c}”), several additional actions are taken to maintain study engagement for all participants. At baseline, all participants receive a study folder including essential information on the study (i.e., a copy of the study information, the informed consent, and insurance information). Additionally, they receive a printed handout displaying all study-relevant contact information, including the study-specific email address and phone number, which are managed by a single study team member (author [name]) and are checked every weekday. Participants are actively encouraged to contact the study team via these contacts for any questions regarding the study. Next, during study participation, the progress of each participant is actively monitored and supervised by an unblinded study team member (author [name]) by keeping an extensive list to monitor and document any protocol deviations, study discontinuations, or other emerging aspects (e.g., CT-relevant queries). By doing so, the study team may actively contact participants to provide support, monitor protocol deviations, and prevent dropouts. Accordingly, if participants withdraw their consent for any reason, the data of these participants will be deleted and not used for any analyses. In case of participant dropout or protocol deviations (e.g., a missing assessment), the previously collected data is still used for analyses, and measures are taken to collect as much data as possible. Following study completion, participants receive a small monetary reimbursement for each completed neuropsychological assessment (25 € per assessment, maximum total of 75 €). Upon request, participants may also receive a short neuropsychological report on the individual results across their completed neuropsychological assessments.

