### Criteria for discontinuing or modifying allocated interventions {11b}

At any time during the study, participants may discontinue participation at their personal request without giving any reason or written statement and without incurring any disadvantage. Specific risks or harms to the participant are not expected during study participation. However, participants might experience temporary fatigue due to the length and efforts of the neuropsychological assessments or CT or may feel distressed when confronted with possible deficits during the neuropsychological assessment or CT. Reported adverse events will be recorded and analyzed, and, if necessary, the protocol will be modified accordingly. A travel and residence insurance policy has been taken out for the duration of the study. In general, study allocation will not be modified retrospectively.

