## Statistical methods

### Statistical methods for primary and secondary outcomes {20a}

The primary analysis is according to the intention to treat, with no exclusions. The change from baseline in the primary outcome MoCA is analyzed by a linear mixed model for repeated measures (MMRM) with fixed effects for baseline, group, time, and group × time interaction (ARH1-structured variance–covariance matrix over time). The primary comparison at T1 (week 9) is based on a pairwise contrast of estimated marginal means with a 95% confidence interval. Secondary outcomes (i.e., further timepoints and measures) are analyzed along the same line, however from an exploratory viewpoint only; thus, no multiplicity adjustment is required. Where available, observed changes will also be interpreted in relation to published minimally clinically important differences (MCIDs) to evaluate clinical relevance in addition to statistical significance.

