### Methods in analysis to handle protocol nonadherence and any statistical methods to handle missing data {20c}

A supplementary per-protocol analysis includes only patients with three valid assessments (i.e., at T0, T1, and T2) and essential adherence to the training schedule (i.e., ≥ 16/20 (80%) completed training days in the experimental group; all control participants). The sensitivity due to missing values of the primary analysis based on MMRM is investigated by reference-based multiple imputation (e.g., jump to reference) [108].

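### Deleting all data of participants who withdraw consent contradicts an intention-to-treat analysis without exclusions, and leaves the denominator of the 14% training-dropout criterion open

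*Protocol article*

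**What the plan says.** Item 18b of the protocol article gives two rules in consecutive sentences. For withdrawal of consent: "if participants withdraw their consent for any reason, the data of these participants will be deleted and not used for any analyses". For other departures: "In case of participant dropout or protocol deviations (e.g., a missing assessment), the previously collected data is still used for analyses".

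Item 20a defines the primary analysis set: "The primary analysis is according to the intention to treat, with no exclusions". The model is an MMRM on change from baseline in MoCA, with baseline as a covariate. Item 20c adds that sensitivity to missing values "is investigated by reference-based multiple imputation (e.g., jump to reference").

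Item 11b states that "participants may discontinue participation at their personal request without giving any reason or written statement".

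The feasibility section lists its measures: "Indicators include CT dropout rate, number of training days completed, total duration of training, and technical handling". It then sets the threshold: "the CT intervention is considered feasible if CT dropouts are ≤ 14" per cent, together with at least 80% of training days and of training time. It does not say over whom the dropout rate is calculated.

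**The concern.** Both rules are current text, and nothing in the article reconciles them. Participants learn their group at the end of the baseline assessment, so any later withdrawal of consent is made with knowledge of the arm. Deleting those records removes randomised participants for a reason that arises after randomisation, which the intention-to-treat statement rules out. The planned imputation cannot examine this loss, because it works on participants who still have a record.

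The second issue is the feasibility claim. If withdrawers are used in no analysis at all, those in the experimental group who stopped training and withdrew consent also vanish from the dropout rate. The feasibility section makes the reading of the efficacy result depend on whether its criteria are met, so the counting rule should be fixed before the data are analysed.

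**Working it through.** **Inputs.** 70 participants planned per arm and 10% planned dropout (item 14); threshold of 14% training dropouts (feasibility section); model and imputation (items 20a, 20c). The planned size is used only as the denominator and is not in dispute: a two-sided t-test at 0.05 with 80% power and d = 0.5 needs 63.77, so 64 per group, as the plan states. The plan rounds the dropout allowance to 70 per group.

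**Step 1: which withdrawals affect which analysis.**

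| Time of consent withdrawal | Primary MMRM on change | Reference-based imputation |
|---|---|---|
| After allocation, before any post-baseline MoCA | No change score exists, so the person contributes nothing whether the data are kept or deleted | Baseline record lost; the person cannot be imputed |
| After a post-baseline MoCA | Observed change scores are removed; the estimate can move | Record lost |

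The model has no baseline-by-group interaction, so the group contrast does not depend on baseline records without follow-up. Deletion therefore alters the primary estimate only in the second row.

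**Step 2: the dropout criterion with everyone counted.** With D training dropouts among N = 70, the rate is D/70.
- 9/70 = 12.86%: passes.
- 10/70 = 14.29%: fails.

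**Step 3: the same criterion under literal deletion.** If w of the D dropouts withdrew consent and are deleted, the rate is (D − w)/(70 − w). For w > 0 and D < 70 this is always below D/70, because (D − w) × 70 < D × (70 − w) reduces to D < 70.

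| Dropouts D | All counted | Deleted w | After deletion |
|---|---|---|---|
| 10 | 14.29%, fails | 1 | 9/69 = 13.04%, passes |
| 12 | 17.14%, fails | 3 | 9/67 = 13.43%, passes |
| 14 | 20.00%, fails | 5 | 9/65 = 13.85%, passes |

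If every dropout withdrew consent, the rate would be 0% whatever the true rate. A participant who finishes training and withdraws later leaves only the denominator, which works weakly the other way: 9/70 would need six such deletions to fail (9/64 = 14.06%).

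**Step 4: chance of meeting the dropout criterion.** Exact binomial sums with N = 70. The true rates and the shares of dropouts who withdraw consent are assumptions, since the protocol gives neither.

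| True dropout rate | No deletion | 25% withdraw | 50% withdraw | All withdraw |
|---|---|---|---|---|
| 14% | 47.5% | 80.0% | 96.7% | 100% |
| 18% | 16.8% | 51.1% | 85.8% | 100% |
| 20% | 8.5% | 36.4% | 76.7% | 100% |

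**The case against.** Four points can be made for the plan.

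*Dropout and withdrawal of consent are separate categories.* A reader might infer from item 11b that nothing tells them apart. That goes too far. Item 18b names both and gives each its own rule, and item 11b speaks of discontinuing participation without saying that this withdraws consent. Its natural reading falls under the rule that keeps the data. The working definition may sit in consent forms or operating procedures that are not shown.

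*The efficacy bias may be negligible.* A reader might infer a material shift in the treatment effect. If 10% of one arm were deleted and differed by 0.5 SD from those retained, that arm's mean would move by 0.10 × 0.5 = 0.05 SD. The documents do not support this as an estimate. It turns the whole planned dropout into consent withdrawals in one arm only, the 0.5 SD has no source, and the deletion rule causes the shift only for people who had already given post-baseline data. Different withdrawal between arms is plausible but not documented: controls are offered free training after follow-up, and the introduction cites adherence of up to 92%.

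*The dropout count can be recovered.* An unblinded team member keeps a list of discontinuations, and allocation lists are stored. A count by arm needs no deleted assessment data. This stands as a means of repair, but the protocol does not say that the count will be made this way.

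*Deletion may be owed to participants.* This also stands. The fault is the unqualified statement of no exclusions and the open denominator, not the right to have data erased.

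**Conclusion.** The contradiction between items 18b and 20a is certain on the text: one consent withdrawal after randomisation makes the intention-to-treat statement untrue. Its numerical effect on efficacy is unknown in size and direction, and it reaches the primary estimate only through people who withdraw after a post-baseline MoCA.

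The feasibility effect is conditional. It needs the literal reading of the deletion rule, and a single deletion changes the result only when dropouts stand at 10 of 70. Among participants who stopped training, the error can only favour the intervention. A reader might infer that the overall feasibility conclusion would be reversed. The documents do not support that, because the criteria on training days and training time must also be met, and missing the criteria leads only to cautious interpretation of efficacy. The point is worth correcting before analysis, and the correction is cheap.

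**What to change.** 1. Define the training dropout rate over all participants randomised to the experimental group. Count every withdrawal of consent before the end of training as a dropout, using the discontinuation list and the allocation records.
2. Treat leaving the study as dropout with data to date retained. Delete data only on an explicit request for erasure, and honour any deletion already promised in signed consent forms.
3. Reword item 20a to cover all randomised participants except those whose data were erased on request, and report the number and timing of erasures by arm.

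The cost is a protocol wording change with ethics notification and one extra entry on the discontinuation log. The second change will do little for people already enrolled under a promise of deletion: this version is dated 26 November 2025 and recruitment was expected to end by the close of that year. The first and third keep their full value until the data are analysed.
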